**Ethical aspects**

Written informed consent shall be taken from the participant or the next of kin.

**Trial management**

Prospective registration in Central Trials Registry India (CTRI) **CTRI/2021/07/035093** on Jul 23, 2021.

*Trial management- By PI*

*Local coordination- By PI*

*Research governance and good clinical practice- shall be followed.*

**Economic evaluation- NA**

**Consumer involvement NA**

**Reporting, Dissemination, and Notification of results**

*Publication policy- Results will be collated and manuscript prepared for submission to a PubMed indexed journal.*

*Disseminating the results- Results will be disseminated in academic meets, social media as per rules.*

**Detailed methodology, with definitions**

**PATIENTS**

- Inclusion: 18 -80 years of age; met all 4 of the following criteria
  - **RR** > 25 breaths per minute; **PaO2/FiO2** < 200mmHg while the patient was breathing oxygen at a flow rate of ≥ 10 liters per minute for at least 15 minutes;
  - **On NIV PSV6 PEEP 5** with < 30% leak**, Minute ventilation > IBW x10mlx25/min** (e.g., for 50 kg individual = 12.5 lpm)
  - **Rule out pain, fever, discomfort**

If any present:

Manage with (when in doubt, all can be given together-)

Injection PCM 1gm- stat for pain/discomfort and /or fever,

Injection Midazolam 1 mg iv stat for anxiety,

Midazolam to be followed by Infusion Dexmedetomidine 400 mcg in 50 ml at 3-5 ml per hour, titrated to blood pressure ( MAP >65 mmHg or and effect.

*And* active patient counseling to comfort and reassure)

**Reassess Minute volume after 30 minutes.**

- Exclusion: PaCO2 ≥ 45 mmHg *and* pH < 7.2; Compensated respiratory acidosis was accepted up to a pH 7.2 according to standard ARDS lung-protective ventilation guidelines *if GCS >12*

Compensated metabolic acidosis with HCO3 < 16mmol/l with sepsis/ acute or chronic renal failure,

Hemodynamic instability (MAP< 65 mmHg) *and* need of increasing doses of vasopressors in last 6 hrs.; GCS <12;

Contraindication to noninvasive ventilation;

Urgent need for intubation (evaluated by the clinician in charge)

Refusal to participate or participate in another study.

Do-not-intubate decision

Epidural catheter block/ dislodged/ less than two doses of the drug could be administered.

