**Trial population**

Trial site(s) and population(s)- COVID ICU patients in AIIMS Bhubaneswar

Inclusion and exclusion criteria- Include- Adult patients with COVID 19 pneumonia 18-80 years of age. Requiring NIV to maintain oxygenation.

Exclusion criteria- Metabolic acidosis HCO3-< 16 or pH < 7.2. Severe hypoxemia warranting cessation of NIV and intubation, non-acceptance of NIV. Chronic opioid user. Uncontrolled sepsis, end of life (EOL) orders.

Sources or methods of recruitment- Daily discussion at 8 am of new admissions to COVID ICU on NIV – assessment for high respiratory drive despite Spo2 > 90 and adequate NIV support

Information for participants- PIS will be provided. Written informed consent will be taken for the patient/ kin of all eligible patients.

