**CRITERIA FOR ENDOTRACHEAL INTUBATION**

The pre-determined criteria for endotracheal intubation and mechanical ventilation (MV) to avoid delayed intubation:

1. Signs of persisting or worsening respiratory failure:

- RR > 40 cycles/min,
- Signs of respiratory-muscle fatigue (no improvement in subjective scores for > 12 hours)
- Copious tracheal secretions,
- SpO2 below 85 % for more than 5 min without technical dysfunction at Fio2 100% and best-tolerated PEEP
- Intolerance to NIV

or one of the following

1. Hemodynamic instability is defined by an SBP below 90 mmHg, MBP below 65 mmHg, or requirement for increasing vasopressor doses to maintain the same for 2 hours.
2. Deterioration of neurologic status with a Glasgow coma scale below 12 points.

For all patients, a trial of HFNO or Nonrebreather oxygen will be allowed according to the physician's preference in patients with signs of persisting or worsening respiratory failure (to rule out patient discomfort with NIV) and no other organ dysfunction before performing endotracheal intubation and invasive ventilation.

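### The haemodynamic exclusion at entry is narrower than the haemodynamic intubation criterion, so on the written rules a patient can be randomised while already meeting that criterion

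*Protocol*

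**What the plan says.** In the Protocol, Detailed methodology, the exclusion list that follows the minute-volume reassessment step removes patients with "Hemodynamic instability (MAP< 65 mmHg) *and* need of increasing doses of vasopressors in last 6 hrs". The conjunction is emphasised, and systolic pressure is not mentioned.

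The section CRITERIA FOR ENDOTRACHEAL INTUBATION uses the same term with a wider meaning: "Hemodynamic instability is defined by an SBP below 90 mmHg, MBP below 65 mmHg, or requirement for increasing vasopressor doses to maintain the same". The sentence ends with a duration, in the words "requirement for increasing vasopressor doses to maintain the same for 2 hours". This item stands outside the group of respiratory signs and is introduced by "or one of the following", so it is sufficient alone. The list is presented as "The pre-determined criteria for endotracheal intubation and mechanical ventilation (MV) to avoid delayed intubation".

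Three other exclusions could catch such a patient: "Urgent need for intubation (evaluated by the clinician in charge"), "Contraindication to noninvasive ventilation" and, in Trial population, "Uncontrolled sepsis, end of life (EOL) orders".

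Intubation is a secondary outcome (Outcome assessment; Statistical analysis), and the intervention stops when it is required (The interventions).

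**The concern.** A rule for entry and a rule for rescue that share a name should share a definition, or the protocol should say why they differ. Here the entry rule needs two signs together and the rescue rule needs one of three. A patient who falls between them is eligible for randomisation and, at the same moment, meets a criterion whose stated purpose is to prevent late intubation.

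Two things are at stake. The first is protection: the patient may be positioned for, and receive, an epidural or sham catheter when the protocol's own list points to intubation. The second is interpretation: an intubation for a state present at entry says nothing about morphine. It would count in the intention-to-treat comparison. If it came before the second dose, the patient would also fall under the fewer-than-two-doses item in the exclusion list.

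**Working it through.** **Inputs.** Exclusion list: excluded = (MAP < 65) and (vasopressor dose rising in the last 6 hours). Intubation criteria: met = (SBP < 90) or (mean pressure < 65) or (vasopressor requirement rising), with two hours attached at least to the last. Each sign is first taken to have lasted two hours or more, so that the criterion is met on either reading of the duration.

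**Step 1: all combinations.**

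| SBP < 90 | MAP < 65 | Vasopressors rising | Excluded at entry | Intubation criterion met |
|---|---|---|---|---|
| no | no | no | no | no |
| no | no | yes | no | yes (gap) |
| no | yes | no | no | yes (gap) |
| no | yes | yes | yes | yes |
| yes | no | no | no | yes (gap) |
| yes | no | yes | no | yes (gap) |
| yes | yes | no | no | yes (gap) |
| yes | yes | yes | yes | yes |

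Seven combinations meet the intubation criterion. The exclusion removes 2 and 7 − 2 = 5 pass. This counts combinations; it is not a share of patients.

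**Step 2: is the conjunction meant?** The same emphasised conjunction joins PaCO2 and pH in the same list, where both are clearly required, because compensated respiratory acidosis is then accepted down to pH 7.2. If the haemodynamic item were instead read as two separate exclusions, low systolic pressure with MAP of 65 or more and no vasopressor rise would still pass: one gap in seven.

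**Step 3: the two-hour wording.** It may govern all three signs or only the vasopressor clause. Systolic pressure is taken as 90 or above unless stated. The last column applies the cross-reference proposed under fix.

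| Case | Excluded now | Criterion met, 2 h on all signs | Criterion met, 2 h on vasopressors only | Excluded after fix (all / vasopressors only) |
|---|---|---|---|---|
| MAP 60 for 3 h, stable dose | no | yes | yes | yes / yes |
| MAP 70, dose rising 3 h | no | yes | yes | yes / yes |
| SBP 85, MAP 66 for 3 h, no rise | no | yes | yes | yes / yes |
| MAP 60, dose rising 1 h | yes | no | yes | yes / yes |
| MAP 70, dose rising 1 h | no | no | no | no / no |
| MAP 60 for 1 h, stable dose | no | no | yes | no / yes |

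The first three cases are gaps on either reading. The last is a gap only if the two hours belongs to the vasopressor clause alone. An added exclusion that wrote two hours against all three signs would leave that case open on the narrower reading; a cross-reference does not.

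**Step 4: size for the intubation outcome.** With 25 per arm (Sample size), one such intubation moves an arm's rate by 1/25 = 4 percentage points. Let k be the number of such patients among 50 and f the share intubated for the entry state whatever the arm. The expected arm difference is then diluted by k × f / 50. Neither k nor f is in the documents, so both are assumed:

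| k | 1 | 2 | 3 | 4 | 5 | 6 |
|---|---|---|---|---|---|---|
| f = 1 | 2% | 4% | 6% | 8% | 10% | 12% |
| f = 0.5 | 1% | 2% | 3% | 4% | 5% | 6% |

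If k = 0 there is no effect.

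**Step 5: the primary sample size.** The protocol's 21 per group reproduces from a 30% fall in a mean of 45, which is 13.5 points, with SD 15, two-sided 5% alpha and an assumed power of 80% (the protocol states none): 20 by the normal approximation, 20.4 by the t-based one, hence 21. No term in it depends on the haemodynamic rule.

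**The case against.** The strongest reply is that the clinician in charge must also judge that intubation is not urgently needed. For the gap to bite, that clinician must see a patient who meets a pre-set intubation criterion and still allow an elective catheter. This carries weight and probably keeps the number small. But the exclusion is a matter of judgement and does not refer to the intubation list, which exists so that the decision does not rest on judgement alone. The exclusion for contraindicated NIV is undefined, and uncontrolled sepsis is only one cause of instability. Dexmedetomidine given before entry is titrated to a MAP above 65, which shows a working floor, but only for patients who receive it and not as an eligibility test.

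A second reply is that other overlaps exist: entry needs a respiratory rate above 25 with no ceiling, while a rate above 40 is an intubation sign. That is so. However, a trial of high-flow or non-rebreather oxygen may come before intubation for respiratory failure without other organ dysfunction, and no such deferral is written for haemodynamic instability. The neurological pair is already aligned, at a Glasgow score below 12 in both places.

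A reader might go further and infer a biased intubation comparison, or a raised catheter risk in these patients. The documents support neither. Allocation is randomised, so such patients are expected equally in both arms, and a chance imbalance would be ordinary sampling error. Nothing in the protocol links these blood-pressure states to catheter complications; its insertion safeguards concern coagulation, platelets and heparin timing.

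**Conclusion.** The mismatch is real on the face of the protocol: five of the seven combinations that meet the haemodynamic intubation criterion pass the haemodynamic exclusion, and only a discretionary exclusion stands reliably in the way. It is a matter of consistency and patient protection, with at most a small effect on one secondary outcome. The 1% to 12% dilution rests wholly on assumed values of k and f, and the true number may be zero. Recording systolic pressure at inclusion and the cause of conversion to invasive ventilation would help to identify many such cases afterwards, though it would not undo a procedure already done. The primary endpoint's sample size is unaffected. The conclusion does not depend on how the two-hour wording is read, but the exact extent of the gap does.

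**What to change.** Keep the existing haemodynamic exclusion unchanged and add to it: *or meeting the haemodynamic criterion for endotracheal intubation at the final pre-randomisation assessment*. In the intubation section, state whether the two hours applies to all three signs or only to the vasopressor requirement. One definition then governs both entry and intubation, and nobody now excluded becomes eligible.

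The cost is one clause and one clarification, using blood pressure and vasopressor doses that the two rules already rely on. A few unstable candidates would become ineligible; the documents do not say how many.

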**The interventions**

A baseline assessment of all outcome measures as appropriate will be made. Normal body temperature, RASS of -1 or 0, and VAS < 4 will be ensured by administering Midazolam ( titrated to effect) or Paracetamol as warranted.

All patients will be turned lateral or sitting position, and an injection of LA be given at L2-3 or L3-4 space. An epidural catheter will be inserted under all asepsis and fixed to the skin in the intervention group. It will be fixed firmly with antimicrobial incise drapes covering at least the lower one-third of the back. For patients who appear fidgety, catheter tunneling may also be used.

The control group will have a sham catheter fixed precisely like the intervention group but not entering the epidural space. The fixation and dressing will be similar to the intervention group.

The intervention group will be administered Injection Morphine Sulphate once every 18-24 hours into the epidural space. The doses will be escalated daily (5-10mg), titrated to the effect: escalation limited by hypoventilation resulting in respiratory acidosis (pH <7.2).

The intervention will continue for a minimum of 2 doses and a maximum of 4 doses (96 hours) of morphine. It will be stopped at 120 hours, or if: the epidural catheter gets dislodged before the second dose, the patient is weaned off noninvasive ventilation to high flow mask for a continuous period of 12 hours or requires endotracheal intubation.

The patient will be followed up till death or 28 days after ICU discharge.

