**Data collection and management**

Data collection- Routine data will be extracted from the ICU records; Study-specific outcome data will be collected every eigh^th^-hour Data collectors will be distinct from the persons administering the epidural morphine/ vs. placebo- (in this case, air)

Photographic evidence will be kept of ventilator parameters, USG of the diaphragm, and subjective comfort and dyspnea scores at each data collection point and sent from inside the COVID ICU to the investigator who is not involved in the patient's clinical care and unaware of group allocation via Whatsapp.

Data entry- Will be done from the photographs and paper Case Report Forms (CRFs) into an Excel sheet by a researcher blinded to the group allocation.

For each time point, representative photographs (de-identified) will be kept for possible crosschecking and data validation as required.

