**EPIDURAL**

Baseline PT/ INR and platelet levels should be within an acceptable range to allow epidural insertion. Insertion catheter between 9 to 2 pm on the given day per the protocolized LMWH given at 7 pm on the units: or at least 4 hrs before the next dose of UFH and 12 hours after the last dose.

**Remove** the **catheter** a minimum of 4 -6 hours after a dose of UFH. Administer the next dose of UFH no sooner than 2 hours after **catheter removal**. Once-daily low-molecular-weight heparin (LMWH).

Daily site inspection (antimicrobial incise drapes transparent dressing) is done each time the drug/ sham injection is made. The injection port is kept well covered and sealed and brought to the side near the flank/ shoulder. The epidural catheters (True or Sham) will be in situ for a minimum of 2 doses or 48 hours, whichever is more, and a maximum of 4days (96 hours of catheter and 120 hours of observation).

All asepsis will be maintained for the control group as in the Intervention group, a Local injection anesthetic will be given at the L2-L3/ L3-L4 site, and the catheter will be taped tightly to the skin and dressing done to match the intervention group.

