**Sample size**

Sample size justification A pilot study showed the mean TFDi in COVID 19 patients on PEEP 5 and clinically optimal pressure support to be 45% (SD 15); To decrease this by 30% at 36 hours after the dose of morphine with allocation in a 1:1 ratio, 21 patients will be needed in each group.

Compliance and missing data- All analyses will be based on the groups as randomly allocated: an intention-to-treat analysis. A per-protocol analysis will also be done. The statistical significance will be taken as the 5% level for the top comparisons and the subsidiary comparisons, the 1% level. Patients with a P/F ratio > 150 at inclusion will be compared to those with lower values.

Data Storage- Because of the unique challenges of repeated data capture in COVID ICU, all repetitive data will be captured photographically and sent to a central data repository online to be categorized and stored by patient name and time of data capture (once every 8 hours), making in 14-time points of data capture for each patient. Data storage will be by blinded personnel.

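### Catheter failure or receipt of fewer than two doses is listed as an exclusion criterion, although it can only arise after randomisation; this contradicts the intention-to-treat rule

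*Protocol*

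**What the plan says.** The protocol's detailed methodology gives an exclusion list (under the heading on reassessing minute volume after 30 minutes). Most entries are baseline conditions, such as acidosis, haemodynamic instability, a low coma score or refusal. The last entry is different: "Epidural catheter block/ dislodged/ less than two doses of the drug could be administered". The shorter exclusion list under Trial population has no such entry.

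The closing Sample size section, under compliance and missing data, sets the analysis populations: "All analyses will be based on the groups as randomly allocated: an intention-to-treat analysis", followed by "A per-protocol analysis will also be done". It does not say which patients form the per-protocol set.

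Two other sections deal with the same events. The interventions section makes dislodgement before the second dose a reason to stop the intervention, together with 12 continuous hours off non-invasive ventilation and intubation, and then follows the patient. The Outcome assessment section records failed insertions and catheter pullouts as outcomes.

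**The concern.** An exclusion criterion decides who enters a trial. This one describes what happens to a patient already in it. If applied as written, it removes randomised patients from the comparison, and the trial no longer has the population that the intention-to-treat sentence promises.

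The removal need not be random. A patient who is intubated or dies before the second dose has had fewer than two doses, and so has a patient who improves enough to be weaned. Intubation and mortality are secondary outcomes and TFdi is the primary one. With 25 patients per arm, the handling of a few such patients can move each of these comparisons.

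**Working it through.** **1. Can the events be known before randomisation?** The type of catheter depends on the allocation: "An epidural catheter will be inserted under all asepsis and fixed to the skin in the intervention group", whereas "The control group will have a sham catheter fixed precisely like the intervention group but not entering the epidural space". Doses are 18 to 24 hours apart. Block, dislodgement and failure to reach a second dose therefore all come after allocation, and the last is known only about a day after the first dose.

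**2. The rules side by side.**

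| Place in the protocol | Treatment of catheter loss or too few doses |
|---|---|
| Detailed methodology, exclusion list | Patient excluded |
| Closing Sample size section | All analyses as randomised; per-protocol analysis in addition |
| The interventions | Dislodgement before dose two stops the intervention; follow-up continues |
| Outcome assessment | Pullouts and failed insertions counted as outcomes |

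The first row cannot be followed together with the second, and it sits badly with the third and fourth. No sentence reconciles them.

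**3. Can the exclusion depend on outcome?** Yes, by three routes before dose two: intubation and 12 hours of weaning (both stopping reasons in The interventions), and death. Intubation and death remove patients who do badly. Weaning removes patients who do well.

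**4. Which arm does it affect?** Read literally, more the morphine arm: "The intervention group will be administered Injection Morphine Sulphate once every 18-24 hours into the epidural space", and only that arm has a catheter that enters the epidural space. Against this, the EPIDURAL section sets the two-dose minimum for true and sham catheters alike, and controls receive injections of air as placebo. The split cannot be computed.

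**5. The plan's own figure.** Inputs from the first Sample size section: mean TFdi 45, SD 15, 30% relative reduction. The difference is 0.30 × 45 = 13.5 points, a standardised effect of 13.5/15 = 0.9. Power and sidedness are not stated. Assuming 80% power and two-sided alpha 0.05, the t-test needs 20.4 per arm, rounded up to 21, which reproduces the plan. The 25 recruited per arm allow for a loss of 1 − 21/25 = 16%. The sample size is not in dispute.

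**6. Illustrative size of the bias.** The protocol gives no catheter failure rate, so these are assumptions: no drug effect, 4 of 25 morphine patients removed, no controls removed. If the removed patients lie d points above the arm mean, the mean of the remaining 21 falls by 4d/21.

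- d = 7.5: 30/21 = 1.4 points, or 11% of 13.5
- d = 15: 60/21 = 2.9 points, or 21% of 13.5
- d = 0: no shift
- d = −7.5 or −15 (for example, early-weaned patients): the same shifts, against morphine

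A simulation of 40,000 null trials, again removing 4 of 25 morphine patients only, varied the correlation between removal and high TFdi. It used the plan's final threshold of 0.04, two-sided:

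| Correlation | Shift in TFdi (points) | Type I error (nominal 4%) |
|---|---|---|
| 0 | 0 | 3.9% |
| 0.3 | −1.25 | 4.8% |
| 0.5 | −2.1 | 6.4% |
| 1.0 (the extreme) | −4.2 | 15.7% |

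**7. Is power the problem?** No. With the full 13.5-point effect, 20 morphine patients against 25 controls still gives 80.8% power at 0.04, compared with 85.5% for 25 against 25. The damage from removal is bias.

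**The case against.** The strongest reply is that the line is a per-protocol criterion put in the wrong list. The only stated rule on analysis populations is intention-to-treat. Early catheter loss stops treatment but not follow-up. The section on respiratory drive continues the assessments for the longer of catheter time and five days, so these patients would still be measured. This is plausible and may be what was meant. But the protocol does not say so, and a reader who applies its exclusion list would drop the patients.

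Three stronger readings are tempting, and the document does not support them.

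- **The loss falls on the morphine arm alone.** This is an inference from the wording about the drug. A sham catheter can also come loose, a control who is intubated early also misses a second sham injection, and blinding of the treating team makes a one-arm rule hard to operate at the bedside.
- **The bias favours morphine.** Losing early intubations and deaths from that arm would favour it, but losing early-weaned patients would work against it. Block and dislodgement may be mechanical and unrelated to TFdi. Similar losses in both arms would bring the shift towards zero.
- **Coagulation results cause a further one-sided loss after allocation.** The EPIDURAL section says "Baseline PT/ INR and platelet levels should be within an acceptable range to allow epidural insertion". It calls the values baseline, and nothing places the check after allocation or limits it to one arm.

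What remains is the contradiction and the possible dependence on outcome. Neither requires the loss to be one-sided.

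**Conclusion.** The point holds as an internal contradiction that needs correction. Events after randomisation are listed as exclusions, in conflict with the intention-to-treat rule and with the sections that treat the same events as a stopping reason and an outcome. If the line were followed, patients could leave the analysis because of intubation, weaning or death.

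The size is conditional. The shift of 1.4 to 2.9 points rests on assumed numbers: 4 removals, all from the morphine arm, all 7.5 to 15 points above the mean. It is zero if removal is unrelated to TFdi and changes sign if the removed patients were doing well. The document fixes neither the direction nor the magnitude.

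**What to change.** Delete the line from the exclusion list and use it only to define the per-protocol set, worded so that the same rule applies to true and sham catheters and to drug and sham injections. State that every randomised patient stays in the allocated arm for the main analyses of TFdi, intubation, mortality and safety, whatever happened to the catheter and however many doses were given.

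This is a change of wording. The statistical cost is dilution by patients who received little drug. If 4 of 25 morphine patients gained nothing (an assumption), the expected difference would be 13.5 × 21/25 = 11.3 points, and power at 0.04 would fall from 85.5% to 71.2%. With 2 such patients it would be 79.1%. The per-protocol analysis remains available as a supplement.

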**Allocation of interventions**

Methods for randomization and stratification- The study research assistant will keep a central random numbers list. She will randomize according to the list available.

Methods for concealment of allocation- An opaque sealed envelope concealing the allotted randomization code will be dispatched to the ICU team.

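### The exclusion list contains an event known only after allocation (catheter failure or fewer than two doses), in conflict with the intention-to-treat rule

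*Protocol*

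**What the plan says.** Three parts of the protocol deal with a patient whose catheter fails or who is not dosed twice.

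- **Detailed methodology, Exclusion list** (under *Reassess Minute volume after 30 minutes*): "Epidural catheter block/ dislodged/ less than two doses of the drug could be administered". It stands beside baseline criteria such as pH, GCS and haemodynamic instability.
- **The interventions**: treatment stops if "the epidural catheter gets dislodged before the second dose", and also on weaning off NIV for 12 continuous hours or on intubation. These are reasons to stop dosing. Nothing in that section removes the patient from the trial.
- **Sample size, in the Detailed methodology** (paragraph on compliance and missing data): "All analyses will be based on the groups as randomly allocated: an intention-to-treat analysis". The next sentence adds: "A per-protocol analysis will also be done". The protocol does not define the per-protocol set.

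Morphine is given once every 18 to 24 hours, for two to four doses. In the other arm, "The control group will have a sham catheter fixed precisely like the intervention group but not entering the epidural space".

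**The concern.** An exclusion criterion should be decidable before allocation. This one is not. If staff or the analyst apply it as written, patients are taken out after randomisation and the groups compared are no longer those that randomisation formed.

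The reasons for removal need not be neutral. A patient who improves quickly and comes off NIV, or who deteriorates and is intubated, before the second dose has had fewer than two doses. Removal can then depend on the course of the disease, which is related to TFdi, the primary outcome. A catheter in the epidural space and one taped to the skin may also block or come loose at different rates. In a trial of 25 per arm, a few such removals could bias the primary comparison.

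**Working it through.** **1. When can the item be known?** Whether the catheter is true or sham depends on allocation, so its block or dislodgement comes after allocation. The second dose follows the first by 18 to 24 hours, so a missed second dose is known only about a day into treatment. No part of the item can be judged at screening.

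**2. How do the three places treat the same patient?** Take a patient whose catheter is dislodged after one dose.

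| Place | Consequence |
|---|---|
| Exclusion list | excluded |
| The interventions | dosing stops |
| Compliance and missing data | analysed in the allocated group |

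The second and third agree with each other. The first cannot be followed together with the third.

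**3. The plan's own sample size.** Inputs from Sample size: mean TFdi 45%, SD 15, a 30% relative decrease, 1:1 allocation, 21 per group needed, 25 recruited. Power and sidedness are not stated; 80% power and two-sided 5% are assumed here.

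- Planned difference: 0.30 × 45 = 13.5 points, or 13.5/15 = 0.9 SD.
- Patients per group: 20 by the normal formula; 20.4, rounded up to 21, by the t-test. The 21 is reproduced.
- Allowance for losses: 25 − 21 = 4 per arm, or 4/25 = 16%.

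The sample size is not in question. It supplies the scale for the next step.

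**4. How far could removal shift the comparison?** Suppose k of 25 patients in one arm are removed, and their TFdi would have differed by d points from that of the other 25 − k. The mean of all 25 equals the mean of the rest plus k × d/25. Removal therefore shifts that arm's mean by k × d/25. If the other arm loses nobody, the between-arm difference shifts by the same amount.

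Both inputs are assumptions. I take k from 1 to 4, where 4 is the protocol's whole allowance for one arm, and d from 0.5 to 1 SD (7.5 to 15 points).

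| Removed (k) | d = 7.5 | d = 15 | Share of 13.5 points |
|---|---|---|---|
| 1 | 1 × 7.5/25 = 0.3 | 1 × 15/25 = 0.6 | 2% to 4% |
| 2 | 2 × 7.5/25 = 0.6 | 2 × 15/25 = 1.2 | 4% to 9% |
| 4 | 4 × 7.5/25 = 1.2 | 4 × 15/25 = 2.4 | 9% to 18% |

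The direction is unknown. Removing early weaners and removing early intubations could push the mean opposite ways, and similar removals in both arms would partly cancel.

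**The case against.** The strongest defence is that the item is a misplaced per-protocol criterion: the protocol plans such an analysis, and its rule for early dislodgement fits that reading. This is plausible, but the protocol does not say it. The heading over the item is Exclusion, and a reader who follows it breaks the intention-to-treat rule. This is not a detail left to an analysis plan, because two statements in the protocol disagree. It can also be said that the words about what could be administered mean technical failure only, not weaning or intubation. The text allows that narrower reading but does not fix it, and technical failure may still differ between catheter types.

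Three stronger readings are tempting and are not supported.

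- **That the exclusion applies to morphine patients only.** A reader might infer this from the reference to doses of the drug, and from the EPIDURAL section, where site inspection "is done each time the drug/ sham injection is made". The same section, however, applies the two-dose minimum to true and sham catheters alike, and a taped sham can also be dislodged. Only unequal rates can be argued.
- **That patients unfit for an epidural will be randomised and then lost from the morphine arm.** The protocol says "Baseline PT/ INR and platelet levels should be within an acceptable range to allow epidural insertion", and neither exclusion list repeats this. But it calls the values baseline, does not place the check after allocation, and refers the study flow to a figure that is not reproduced in the text at hand. Nothing links a failed check to the two-dose item.
- **That the trial loses power because undosed patients dilute the effect.** Such dilution comes with intention to treat, which the protocol already prescribes and the remedy keeps. It does not measure this defect.

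**Conclusion.** The point holds as a conflict within the protocol. A post-allocation event is listed as an exclusion criterion, against the rule that analyses follow the randomised groups and against the section that treats early dislodgement as a stopping reason only. That much rests on the text alone.

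The size of the possible bias does not. With the assumed 1 to 4 removals in one arm, none in the other, and a 0.5 to 1 SD difference, the shift is 0.3 to 2.4 points. The upper end needs the whole loss allowance of one arm to fall under this item. The protocol gives neither a rate of under-dosing nor any indication of direction, so these figures show a scale and are not a forecast. If the intention-to-treat rule is followed and the exclusion ignored, this bias does not arise. The correction should be made because the protocol leaves that choice open.

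**What to change.** 1. Delete the item on catheter block, dislodgement and fewer than two doses from the exclusion list.
2. Use it to define the per-protocol set, with the same rule in both arms and sham injections counted as doses in the control arm. Say whether doses missed because of weaning or intubation count.
3. State that the primary intention-to-treat analysis of TFdi keeps every randomised patient, whatever the number of doses received.

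This costs a few lines of wording, with no new data and no change to the sample size.

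An optional clarification, not a correction of an error shown by the text: list PT/INR or platelets outside the accepted range as an exclusion, checked in all patients before the envelope is opened. Allocation of interventions says only "An opaque sealed envelope concealing the allotted randomization code will be dispatched to the ICU team" and does not place the check before or after that step. The tests are already planned at baseline, so the cost is at most a few candidates excluded at screening.
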